### Serious Game App Intervention

#### App Development

The “SteWARdS Antibiotic Defence” app was developed in collaboration with Temasek Polytechnic, a public tertiary institution in Singapore. The study intervention involves the completion of a quest in the “SteWARdS Antibiotic Defence” app. Participants are required to respond to 11 baseline knowledge items before they can begin the game quest. The game quest involves passing all levels of 2 minigames (ie, Tower Defence and Match3), while the third game (ie, Endless Runner) allows participants unfamiliar with the game mechanics to earn extra coins to complete the intervention within the stipulated time frame.

Completing the baseline knowledge items is a prerequisite to proceed to the minigames, while completing the postgame knowledge items will fulfill the app intervention. The app will release bite-sized messages to reinforce concepts on the prevention and management of URTI and the appropriate use of antibiotics and AMR through gameplay and interaction with the nonplayer characters in the app. Participants are given only 3 “lives” daily to complete the Tower Defence and Match3 levels. Hence, the game completion may take slightly longer if the participant fails the levels more than 3 times in a day.

#### Evidence-Based Content

Many serious game apps intended for improving user knowledge failed to consider the cognitive process of learning, which limited the effectiveness of the intended outcome of the app. Therefore, we used Bloom’s revised taxonomy [20] as a guide to design the game mechanics. Concepts such as “antibiotics are effective for bacteria and not viruses” are reinforced repeatedly in the minigames to enhance memory. Users have to apply the concepts they learn to advance the game levels. For example, users must eliminate bacteria with the antibiotic turret and viruses with the symptomatic relief medication turret in the Tower Defence game and use the correct weapon to shoot the correct organism in the Endless Runner game. Users will also experience the “cost” of AMR by realizing that “misusing” antibiotic turrets in the earlier levels will drain their resources for tackling the superbug in the final level. Feedback (whether users respond to the items correctly or not) will be provided for the postgame knowledge survey to help users evaluate the concepts they learn from the game quest.

We derived the educational content in the app from a rigorous review of knowledge gaps [9,12,21], antibiotic guidance [22], and inputs from health care professionals. The in-app messages were also adapted to the local context to ensure their relevance to users.

#### Game Components

##### Overview

The app was designed with gamification elements to enhance user engagement and the learning process [23]. Gamification was achieved through clear rules, goal-oriented challenges, and rapid feedback. Users learn about appropriate antibiotic use and effective methods to recover from uncomplicated URTIs by interacting with the nonplayer characters and playing the minigames in the app. The 3 minigames are as follows.

##### Tower Defence

Players are required to build turrets (types of medication) to defend their fort (immunity bar) against enemies (bacteria or viruses) and have to cross 9 levels to complete this game. Players have to choose the appropriate turrets and strategically place them at appropriate locations to effectively target their enemies.

The first 2 levels teach players that antibiotics are effective against bacteria. Players are encouraged to buy and build antibiotic turrets to survive the onslaught of bacteria enemies (Figure 2A). The next 2 levels build on this knowledge by introducing the concept that antibiotics are bacteria specific. There will be 2 different types of bacteria (α-bac and β-bac), and players must build antibiotic turrets (α-mycin and β-cillin) specific to each bacteria enemy to clear the level (Figure 2B).

**Figure 2 figure2:**
[figure not shown]
(A) Scene in the Tower Defence game with bite-sized educational messages. (B) Scene in the Tower Defence game with α-bac, β-bac, and viruses. (C) Scene in the Match3 game with messages for healthy living. (D) Scene in the Endless Runner game. The round icon represents a bacterium.

Levels 5 and 6 educate users that antibiotics are not effective against viruses. New enemies (viruses) are introduced, and players must buy immunity turrets to attack the viruses. To further instill this concept within players, bacteria and virus enemies attack simultaneously in levels 7 and 8, and players need to select the appropriate antibiotic and immunity turrets to complete the levels.

The last level educates players on antibiotic resistance by introducing multidrug-resistant organisms. Players have to invest in an expensive antibiotic turret effective against the multidrug-resistant organisms to complete this level.

The game difficulty increases with the levels, while players must be mindful of the coins they spend when purchasing and upgrading the necessary turrets. The immunity levels of the players are affected when too many enemies reach the end point. Players lose the level when their immunity bar falls to 0.

##### Match3

Match3 attempts to educate players on good health habits. Level 1 encourages participants to get a healthy amount of sleep. Level 2 focuses on the importance of a nutritious diet. The third level emphasizes on immunization, and the last level urges participants to care for their health in a holistic manner. Users are required to match 3 or more tiles within a specific time limit to successfully clear each level (Figure 2C).

##### Endless Runner

This game aims to reinforce the message that antibiotics are only effective against bacteria and not viruses. The player has to dodge obstacles and collect coins while running. An antibiotic gun is effective in shooting away bacteria obstacles, while an immunity gun can be used to shoot virus obstacles. This game also allows players to collect coins for use in the Tower Defence game in an engaging manner (Figure 2D).

### Study Procedures

We will randomize participants who are eligible for the study into the control or intervention group and collect their personal details in a password-protected file. Their demographic information will be collected on FormSG, a trusted web-based form manager developed by the Singapore government to collect survey data securely. We will require all participants to complete a 10-minute baseline KAP survey. For participants randomized into the intervention group, a study team member will assist participants in installing the “SteWARdS Antibiotic Defence” app on their mobile phones and provide further instructions regarding the game quest. Participants will need to complete the game quest in the app within 2 weeks, after which they will need to complete the postgame knowledge and an app satisfaction survey to complete the intervention. Participants will be contacted 6-10 weeks after completing the game quest and be asked to complete a 10-minute postintervention KAP survey.

Control group participants will complete a 10-minute baseline KAP survey and be contacted 6-10 weeks after recruitment to complete another 10-minute KAP survey. Participants will receive personalized messages via WhatsApp with a FormSG survey link and instructions to complete the postintervention survey during the study follow-up. We will provide reimbursement to all participants for their participation in the study. Reimbursement is structured according to behavioral economics principles to motivate participants to complete the intervention [24]. For example, reimbursement is divided over smaller amounts and is tiered to a higher value as the participant completes tasks toward the completion of the study. If the participant withdraws from the study, he or she will be asked to uninstall the app and will not be further contacted other than for reimbursement. The data collected prior to study withdrawal will be used for intention-to-treat analysis.

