**Results:**

The primary study outcome is the change in participants’ KAP toward antibiotic use and AMR 6-10 weeks post intervention or 6-10 weeks from baseline for the control group (web-based survey). We will also assess the knowledge level of participants immediately after the participant completes the game quest (in the app). The secondary study outcomes are the user engagement level (tracked by the app) and satisfaction level of playing the game (via the immediate postgame survey). The satisfaction survey will also collect participants’ feedback on the game app.

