**Conclusions:**

Our proposed study provides a unique opportunity to assess the effectiveness of a serious game app in public health education. We anticipate possible ceiling effects and selection bias in our study and have planned to perform subgroup analyses to adjust for confounding factors. The app intervention will benefit a larger population if it is proven to be effective and acceptable to users.

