#### Secondary Outcomes

The secondary outcomes are the assessment of the user engagement level (tracked by time spent on the app) and satisfaction level of playing the game (via the immediate postintervention survey). The satisfaction survey will also collect participants’ feedback on the game app.

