### Statistical Analysis

We will analyze the changes in the KAP scores with multivariable linear regression models and app satisfaction levels among intervention group participants with descriptive analyses. We will also conduct a post hoc power analysis to ensure that the sample size used in our study is adequately powered to detect a significant change.

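### As described, the satisfaction survey is reached by finishing the quest, so satisfaction reported for the app arm would describe finishers and is likely, though not certain, to overstate it

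*Protocol article*

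**What the plan says.** Three places in the protocol article fix when satisfaction is measured, and they agree.

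- Study Procedures: the quest is to be finished within two weeks, "after which they will need to complete the postgame knowledge and an app satisfaction survey to complete the intervention".
- Abstract, Results: the outcome is "satisfaction level of playing the game (via the immediate postgame survey").
- Secondary Outcomes: the outcome is "satisfaction level of playing the game (via the immediate postintervention survey"). The same survey collects feedback on the app.

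Finishing is a demanding condition. App Development states: "The game quest involves passing all levels of 2 minigames (ie, Tower Defence and Match3"). Game Components describes nine Tower Defence levels of rising difficulty and four timed Match3 levels. Attempts are limited: "Participants are given only 3 “lives” daily to complete the Tower Defence and Match3 levels".

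For a participant who withdraws, Study Procedures says that "he or she will be asked to uninstall the app and will not be further contacted other than for reimbursement". No section describes a satisfaction survey for someone who stays in the trial but does not finish the quest.

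Statistical Analysis plans to summarise "app satisfaction levels among intervention group participants with descriptive analyses". The Abstract's Conclusions give the use of the result: "The app intervention will benefit a larger population if it is proven to be effective and acceptable to users". The closing Conclusions section repeats the two conditions, effectiveness and acceptability.

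**The concern.** Whether a participant answers the survey depends on success with the product being rated. People who find the game too hard, dull or awkward are more prone to stop before the survey appears, and their opinion and feedback are then missing. What remains is a summary of those who passed every level, under a label that names the intervention group.

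Two things are at stake. User satisfaction is a stated secondary objective, and wider use of the app is linked to its being acceptable. A wider public would include people who cannot or do not wish to finish, and their comments would be among the most useful for improving the app. The article itself recognises, under Potential Limitations, that less technologically able older adults may have trouble finishing.

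**Working it through.** **What can be reproduced.** The article states no quest-completion rate, no expected satisfaction level and no threshold for acceptability, so there is no planned figure to check on this point. The only stated loss is the 30% attrition in Sample Size. That is loss to the study, not failure to finish the quest, and it is borrowed below only as a stand-in.

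**Inputs**

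- App arm: N = 200 (Sample Size).
- Completion proportion: c = 0.70 (assumed, as 1 − 0.30), so 200 × 0.70 = 140 finishers. All are assumed to answer.
- Satisfaction among finishers: s_F = 0.80 (assumed), so 140 × 0.80 = 112 satisfied.
- Satisfaction among non-finishers: s_N, unobserved, allowed to run from 0 to 1.

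**Formulas**

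Arm-wide satisfaction = c × s_F + (1 − c) × s_N

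Error of the finisher-only figure = s_F − arm-wide = (1 − c) × (s_F − s_N)

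**Results at c = 0.70, s_F = 0.80** (finisher-only figure 80%)

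| s_N | Arm-wide | Error of the 80% figure |
|---|---|---|
| 0 | 0.56 + 0.30 × 0 = 56% | 24 points too high |
| 0.40 | 0.56 + 0.30 × 0.40 = 68% | 12 points too high |
| 0.60 | 0.56 + 0.30 × 0.60 = 74% | 6 points too high |
| 0.80 | 0.56 + 0.30 × 0.80 = 80% | none |
| 1 | 0.56 + 0.30 × 1 = 86% | 6 points too low |

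In counts, the bounds are 112/200 = 56% and (112 + 60)/200 = 86%.

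**Sensitivity**

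- If no non-finisher is satisfied and s_F stays at 0.80, the error is (1 − c) × 0.80: 8 points at 90% completion, 16 at 80% and 40 at 50%.
- With s_F = 0.90 and c = 0.70, the arm-wide range is 0.63 to 0.63 + 0.30 = 0.93, so the 90% figure would be from 27 points too high to 3 too low.

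The sign of the error depends only on whether non-finishers are less satisfied than finishers. Its size depends on that gap and on the completion proportion, and the article gives neither.

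**The case against.** Several counterarguments have weight.

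- **Non-finishers are not expressly excluded.** Study Procedures describes the intended path and bars further contact only for people who withdraw. A fuller protocol may say how the others are followed up. It is therefore tempting, but wrong, to say that the plan rules out surveying non-finishers. Even so, the timing is stated in three places and always follows the quest. This is a stated time point that selects respondents, not merely an omitted detail.
- **The direction is not certain.** A reader might infer that satisfaction will be overstated. The documents do not establish that. Reimbursement rises as tasks are completed and may keep dissatisfied users playing. Endless Runner lets people unfamiliar with the mechanics earn coins so that they can finish in time. Some will stop for lack of time and not from dislike. Overstatement is the more likely direction, but it remains an inference.
- **The label fixes no denominator.** The wording in Statistical Analysis may only identify the arm that has the app, so it cannot be read as a claim that the whole arm will answer. It nevertheless gives no signal that the respondents would be finishers.
- **Acceptability need not rest on this survey.** A reader might infer that the roll-out decision depends on it alone. The closing Conclusions say only that the team may incorporate the app, under two conditions and with no criterion. Time in the app is a second user outcome and does not require finishing. Time, however, measures engagement and can rise when a struggling player repeats levels, so it does not stand in for the missing answers.
- **Partial mitigation exists.** Potential Limitations promises to report recruitment and follow-up problems and to compare older with younger participants. It does not mention satisfaction.

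**Conclusion.** The point holds in a limited form. As the procedures are described, the satisfaction and feedback survey is reached by completing the quest, and no route is given for app-arm participants who do not finish. The reported outcome would therefore describe finishers. It is likely, though not certain, to overstate satisfaction across the arm.

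The size cannot be derived from the article. The range of 24 points too high to 6 points too low rests on an assumed 70% completion, an assumed 80% satisfaction among finishers, and full response from finishers. It shows how little a finisher-only figure pins down the arm and is no estimate of the bias.

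This concerns a descriptive secondary outcome. It affects neither the KAP comparison nor the sample size. It is still worth correcting, because acceptability is named as a condition for wider use and the repair is small.

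**What to change.** 1. At the two-week quest deadline, send the satisfaction and feedback survey by the WhatsApp and FormSG route already used for follow-up to all app-arm participants who have not withdrawn, whether or not they finished.
2. For those who withdraw, offer the survey only at the moment of withdrawal, so that the rule against later contact is kept.
3. Report the numbers assigned, started, finished and answered.
4. Give satisfaction among respondents, split by finished and not finished. Show best-case and worst-case bounds for non-responders. Do not take all assigned participants as the denominator of a single headline figure, since that counts every non-responder as dissatisfied.
5. If non-finishers cannot be surveyed, label the outcome *satisfaction among completers*, print the completion proportion beside it, and do not use it alone to support a statement that the app is acceptable.

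The cost is a small extra messaging effort. Response from non-finishers will be incomplete, and the headline satisfaction figure will probably be lower.

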## Methods

### Study Design

Our study is a parallel 2-armed randomized controlled trial (RCT) assessing the effectiveness of a serious game app in increasing the knowledge and changing the attitudes and perceptions about appropriate antibiotic use and AMR among the public. Participants randomized to the intervention group will be asked to download and complete the quest in the “SteWARdS Antibiotic Defence” app within 2 weeks on their smartphones. “SteWARdS Antibiotic Defence” is an evidence-based serious game app developed by the study team. The app will deliver bite-sized information on (1) the management of upper respiratory tract infections (URTIs), (2) appropriate antibiotic use, and (3) development of AMR to users as they complete the game quest (refer to the section on “Serious Game App Intervention”). Participants randomized to the control group will not be required to download the app. All participants will be followed up for 6-10 weeks to assess the effects of short-term knowledge retention. The design of the trial is presented in Figure 1.

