### Outcome Measures

#### Primary Outcomes

The primary outcome is the change in participants’ KAP toward antibiotics use and AMR 6-10 weeks post intervention from the baseline, measured by the KAP survey. We developed the KAP survey by assessing the literature [9,21,25] and adapting questions from the World Health Organization’s multicountry public awareness survey on antibiotic resistance [12]. Our KAP survey comprises 11 knowledge items with binary responses and 14 three-point Likert-scale items assessing participants’ attitudes and perceptions on antibiotics use and AMR (Table 1). We reverse-scored a few knowledge items in the postgame and postintervention surveys to reduce memory effects on knowledge gains.

**Table 1 table1:** Knowledge, attitudes, and perception survey items.

Item number			Items		Response options
**Knowledge items**					True and false
	1	If bacteria are resistant to antibiotics, it can be very difficult or impossible to treat the infections they cause.			
	2	It is okay to buy the same antibiotics or request for them from a doctor, if they had helped you get better previously when you had the same symptoms.			
	3	It is okay to use antibiotics that were given to a friend or family member, as long as they were used to treat the same illness.			
	4	I can stop my antibiotics course when I start feeling better.			
	5	Antibiotic resistance is an issue that could affect me or my family.			
	6	Antibiotic resistance is only a problem for people who take antibiotics regularly.			
	7	Many infections are becoming increasingly resistant to antibiotics treatment.			
	8	Antibiotic resistance is an issue in other countries and in Singapore.			
	9	Antibiotic resistance occurs when your body becomes resistant to antibiotics and antibiotics no longer work as well.			
	10	Bacteria which are resistant to antibiotics can spread from person to person.			
	11	Antibiotic-resistant infections could make medical procedures like surgery, organ transplant, and cancer treatment much more dangerous.			
**Statements on attitudes and perceptions**					Agree, disagree, and unsure
	12	I feel that there is no harm in taking antibiotics.			
	13	I need antibiotics to help me to recover faster from the common cold and flu.			
	14	I need antibiotics to help me to recover from serious symptoms of the common cold and flu.			
	15	I need antibiotics if I continue to have flu symptoms after 2 weeks.			

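### The primary survey is dated from quest completion in the intervention arm and from recruitment in the control arm, so intervention participants who never finish have no stated survey date

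*Protocol article*

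**What the plan says.** All references are to the protocol article.

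- **Intervention arm, Study Procedures:** "Participants will be contacted 6-10 weeks after completing the game quest and be asked to complete a 10-minute postintervention KAP survey". The time allowed for the quest is given just before: "Participants will need to complete the game quest in the app within 2 weeks".
- **Control arm, Study Procedures:** participants will "be contacted 6-10 weeks after recruitment to complete another 10-minute KAP survey".
- **Abstract, Results:** the same split, with the outcome taken "6-10 weeks post intervention or 6-10 weeks from baseline for the control group (web-based survey").
- **Primary Outcomes:** "The primary outcome is the change in participants’ KAP toward antibiotics use and AMR 6-10 weeks post intervention from the baseline". No separate anchor is given here for controls.
- **Study Design:** "All participants will be followed up for 6-10 weeks to assess the effects of short-term knowledge retention". No starting point is named.
- **End of the intervention:** App Development says that "completing the postgame knowledge items will fulfill the app intervention". Study Procedures places the satisfaction survey at the same point, after the quest: "after which they will need to complete the postgame knowledge and an app satisfaction survey to complete the intervention".

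Study Procedures deals separately with withdrawal: those who withdraw are contacted again only for reimbursement, and their earlier data enter an intention-to-treat analysis. Potential Limitations expects that some eligible older adults may struggle to finish the quest.

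**The concern.** Finishing the quest happens after randomisation and exists in one arm only. If it triggers the primary survey, being measured depends on behaviour in the intervention arm but not in the control arm. Finishing is also a real hurdle: 9 Tower Defence levels and 4 Match3 levels, 13 in all, with 3 lives a day and 2 weeks allowed.

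A participant who stalls without withdrawing is still in the trial, yet the text gives no date on which to send the survey. If such people are not surveyed, the primary comparison sets finishers against all controls and no longer rests on randomisation alone. Regression adjustment can correct only for measured differences, and a survey that was never sent cannot be recovered at analysis.

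A second, smaller consequence is that the two arms are measured at different times from recruitment.

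**Working it through.** **1. Survey dates under the text as written**

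| Participant | Anchor | Weeks from recruitment |
|---|---|---|
| Control | recruitment | 6 to 10 |
| Intervention, finishes on time | quest completion (0 to 2 weeks) | 0 + 6 = 6 to 2 + 10 = 12 |
| Intervention, does not finish, does not withdraw | none stated | undefined |

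For on-time finishers the intervention window ends at most 2 weeks later than the control window, and the two overlap from week 6 to week 10. The third row is the main point.

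**2. The plan's own figures (Sample Size section)**

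A two-sided t-test with effect size 0.334, alpha 0.05 and 80% power needs 141.7, rounded up to 142 per group, as stated. With 30% attrition, 142/0.7 = 203, against 200 planned; 200 x 0.7 = 140 evaluable per group gives 79.5% power. These figures are not in dispute and only set the scale.

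**3. How large could the bias be if non-finishers were not surveyed?**

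The article gives no completion rate and no correlations, so everything here is assumed. Let finishing depend on a normally distributed liability, with p the share finishing, r_F and r_B its correlations with the follow-up and baseline scores, and equal SDs at both times. Take control loss as non-selective. Finishers then have a mean liability of k = phi(a)/p, where P(Z > a) = p.

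For p = 0.7: a = -0.524, phi(a) = 0.348, k = 0.348/0.7 = 0.497.

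- *Follow-up score only*, r_F = 0.3: 0.3 x 0.497 = 0.149, about 0.15 SD.
- *Baseline-adjusted*, r_F = r_B = 0.3, baseline-to-follow-up correlation 0.6: (0.3 - 0.6 x 0.3) x 0.497 = 0.12 x 0.497 = 0.060, about 0.06 SD.
- *Change score*, r_F = r_B = 0.3: (0.3 - 0.3) x 0.497 = 0.
- *Change score*, r_F = 0.2, r_B = 0.3 (for example, if a ceiling limits gains): (0.2 - 0.3) x 0.497 = -0.05 SD, against the app.
- *Change score*, r_F = 0.3, r_B = 0 (finishing unrelated to baseline): 0.3 x 0.497 = 0.149, about 0.15 SD in favour of the app.

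For p = 0.9: k = 0.175/0.9 = 0.195. The first two results fall to 0.3 x 0.195 = 0.06 SD and 0.12 x 0.195 = 0.02 SD.

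Against the planned 0.334, 0.15 SD is 45% (0.149/0.334) and 0.06 SD is 18% (0.060/0.334). Under equally arguable assumptions the bias may be material, negligible or reversed.

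**The case against.** The strongest reply is that the article nowhere says non-finishers go unsurveyed. Study Design says all participants are followed up, the survey link is described as going to participants without a completion condition, only those who withdraw are said not to be contacted again, and intention-to-treat is named. The completion trigger may simply describe the expected path of a compliant user. The trial schedule figure is not available here, and the full protocol may hold a fallback date. This stands as far as intent goes: exclusion is an inference. It does not supply a date. The Study Design sentence names no start point, and the Abstract and Primary Outcomes both use a post-intervention anchor.

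Dating the survey from the end of play can also be defended, because the stated aim is short-term retention. A later survey allows more forgetting, which if anything works against the app. That largely disposes of the interval difference as a concern in its own right.

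A reader might go further and infer that the trial will compare selected finishers with all controls and so favour the app. With 140 per arm the standard error is sqrt(2/140) = 0.1195 SD, and a bias of 0.149 SD would give an ineffective app a P(Z > 1.96 - 1.25), or about 24%, chance of being declared effective instead of 2.5%. The documents do not support this as a finding. It models the follow-up score, whereas the outcome is change from baseline analysed by multivariable regression. It treats all control loss as non-selective, although controls answer the same self-completed survey. It also rests on an assumed finishing rate and correlation. With the baseline adjustment assumed above, the standard error is 0.1195 x sqrt(1 - 0.36) = 0.0956 and the chance is about 9%.

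A reader might likewise see a flaw in the trial's result because only finishers rate the app. Satisfaction is a descriptive secondary outcome within one arm, so this does not touch the randomised comparison.

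**Conclusion.** The concern holds as a gap in a stated rule. The article ties the primary survey to finishing the quest in one arm and to recruitment in the other, gives no date for an intervention participant who neither finishes nor withdraws, and so conflicts with its own statements on follow-up of all participants and intention-to-treat analysis. Followed literally, it makes measurement of the primary outcome depend on a post-randomisation behaviour in one arm.

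The consequence is possible, not established, and its direction is open. The illustrative values run from -0.05 to 0.15 SD with 70% finishing and are smaller with 90% finishing. All rest on assumed completion rates and correlations, on non-finishers in fact going unsurveyed, and on non-selective loss among controls. The difference in interval, at most 2 weeks with overlapping windows, is secondary.

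This should be fixed: the remedy is cheap, and unsent surveys cannot be made good later.

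**What to change.** - Count one common survey window from randomisation in both arms, for example the present window shifted by the 2-week quest period for everyone: 6 + 2 = 8 to 10 + 2 = 12 weeks.
- State that the survey link goes to every randomised participant who has not withdrawn, whether or not the quest was finished.
- Align the Abstract (Results), Study Design, Study Procedures and Primary Outcomes with that rule.
- Optionally, send the satisfaction survey to the whole intervention arm when the 2-week period ends, and report it by completion status.

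The cost is protocol wording and a changed send date for the messages. The drawback is that time since the end of play will vary by up to 2 weeks more among finishers, so retention is timed slightly less precisely. If staff already survey everyone, the change only puts existing practice in writing.
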